### Interventions

The subjects that enter the tens -group will be asked to apply the tens therapy for at least 40 minutes continuously per day during 6 weeks. All patients in the intervention group will be informed that the intensity should be high enough so that an unpleasant but non-painfull sensation is acquired. The settings of the current will not change during the study. The patients that are assigned to the sham tens treatment will receive an inactive placebo tens therapy using a nonfunctional unit that appears to work but provides no stimulus. To blind the investigator as well as the patient, the sham tens device will deliver current for 30 seconds and then ramps down to no current. This approach has been studied and has been proven effective in blinding subjects and investigators to eliminate expectation bias [34]. All participants will be told that they may not feel anything after a while but that this does not mean that the machine is not working. All patients will be asked to come back after two and four weeks to assess their ability to precisely replicate the tens installation.

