**Methods:**

Patients with knee pain due to OAk will be recruited through advertisements in local media. Temporal summation, before and after a heterotopic noxious conditioning stimulation, will be measured. In addition, pain on a numeric rating score, WOMAC subscores for pain and function and global perceived effect will be assessed. Patients will be randomly allocated to one of two treatment groups (tens, sham tens). Follow-up measurements will be scheduled after a period of 6 and 12 weeks.

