### Sensitization in relation to the effect of tens

The effectiveness of tens on knee pain in OAk patients is unclear, due to conflicting results [13]. The ambiguous results of the included studies could be due to the inclusion of heterogeneous types of patients. One important feature distinguishing patient groups might be the presence of central sensitization.

In case of central sensitization, the response to peripheral stimuli, e.g., electrical stimuli as well as mechanical pressure, cold, heat, light, sound and chemical substances is enhanced [26]. Tens (Burst) currents influence pain through the electrical stimulation of low-threshold A-beta cutaneous fibers. This stimulation might enhance the responsiveness of central pain-signaling neurons of OAk patients who are centrally sensitized. In these patients an adverse effect of tens on the pain perception can be expected. The identification of potential subgroups of sensitized and non-sensitized symptomatic OAk patients is needed, as they can react differently to tens. So far, the presence of central sensitization has not been considered as a confounding factor in studies assessing the pain inhibitory effect of burst tens on OAk.

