### Sample size

Sample size calculation is based on data from Law and Cheing [30]. They found a significant difference in the reduction of pain (2.9(4.7) points on a 0-10 VAS) when applying a tens current (pulse width: 200 μs, frequency: 100 Hz) on the knee of patients with OAk compared to a control group not receiving tens treatment. In this study the response within each subject group was normally distributed with standard deviation 4.7. If the true difference in the experimental and control means is 2.9, we will need to study 42 experimental subjects and 42 control subjects to be able to reject the null hypothesis that the population means of the experimental and control groups are equal with probability (power) 0.8. The Type I error probability associated with this test of this null hypothesis is 0.05. To take into account a 15% loss of data sample size is inflated up to 50 per group (n/0.85). Sample size is augmented by 10% per potential confounding factor (i.e. age and sex) [31]. The total sample size to be recruited will be 120 subjects.

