### Follow up

During the 6 weeks following the first appointment, a study nurse will contact the participants of the tens and stens groups weekly by telephone. Subjects will be asked about any inconvenience with the handling of the tens device as well as if they have received other treatments.

After 6 and 12 weeks participants will be asked to rate their GPE, as well as KPa, KPp, WOMAC and medication use. At these occasions *Pressure pain threshold, temporal summation (TS) and *Diffuse noxious inhibition control (DNIC) will be assessed as well.

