### Data reduction and Statistical analysis

An intention-to-treat analysis will be performed so that the integrity of the randomization is ensured. Normality will be checked via the Shapiro-Wilk test.

To ensure good balance of participant characteristics in each group at baseline, stratification is used [39]. Changes in differences between both treatment groups after the intervention period (at 6 w and 12 w) will be analyzed using repeated measures ANOVA for the following variables: KPp, KPa, WOMAC subscores for pain and function, GPE. If the modulus of the partial correlation of potential confounding factors age and sex with the primary outcome values equals minimum 0.3, these covariates of prognostic values will be added as covariates in the ANOVA model [40].

As a secondary analysis, a linear regression analysis will be used with the following dependent factors: BMI, TS and DNIC; and as independent factors: KPa, KPp, WOMAC subscales for pain and function.

Significance value for all tests will be set at p < 0.05. All analyses will be performed using SPSS 20 for Windows.

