## Discussion

This study has a double aim. First, to explore the pain inhibitory effect of tens in OAk patients. Second, to assess whether components of central sensitization like temporal summation and diffuse noxious inhibitory control, affect this pain inhibitory effect.

It is believed that tens influences pain through different pathways. One of these pathways is the gate-control theory [9]. The second goal of our study protocol, i.e. exploring the potential prognostic value of TS and DNIC on the pain inhibitory effect of tens, is based on this rationale. However, opioid pathways that involve peripheral, spinal and supraspinal mechanisms [41,42] are also proposed as an explanation for the pain modulation of tens and this pathway may be less vulnerable for an adverse effect of tens in central sensitized OAk patients.

As tens may influence pain through the electrical stimulation of low-threshold A-beta cutaneous fibers, the responsiveness of central pain-signaling neurons of OAk patients who are centrally sensitized is augmented to the input of these electrical stimuli. This would encompass an adverse therapy effect of tens on the pain perception in patients with OAk who are centrally sensitized. Therefore we think that it might be interesting to identify a subgroup of symptomatic OAk patients, i.e., non-sensitized patients, who are likely to benefit from burst tens.

The majority of studies that were published in the past and that focused on treatment effects of tens, embody currents that were administered by a therapist in a practice or hospital setting. As portable tens devices are marketed as small, inexpensive, easy-to-use home units [13], we choose to use a self-administered protocol. This approach may encompass a positive influence on the patient's participation to the treatment as well as to the cost effectiveness of the treatment, as the machines that are used in (professional) practices are far more expensive than these portable tens devices.

To assess whether dose-effects may influence the treatment outcome, we plan to record the daily duration of the electro stimulation that is applied.

One major concern when using self-administered medical care is treatment adherence. We think that a weekly phone call after the initial start of the study may improve treatment adherence as well as stimulate participants to consistently fill out the diary.

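### Rating pain at the existing week-2 and week-4 visits would be a cheap improvement: as planned, a patient lost before week 6 has no scheduled post-baseline pain score

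*Protocol article*

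**What the plan says.** Under Interventions, every patient in both arms is invited to two visits during the six-week course: "All patients will be asked to come back after two and four weeks to assess their ability to precisely replicate the tens installation". That is their only stated purpose.

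The outcome schedule is under Follow up: "After 6 and 12 weeks participants will be asked to rate their GPE, as well as KPa, KPp, WOMAC and medication use". The abstract agrees: "Follow-up measurements will be scheduled after a period of 6 and 12 weeks".

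Two other contacts fall before week 6, and neither is said to include a pain score:

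- Weekly telephone calls (Follow up): "Subjects will be asked about any inconvenience with the handling of the tens device as well as if they have received other treatments".
- The home recording described in the Discussion: "we plan to record the daily duration of the electro stimulation that is applied".

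The analysis section plans a repeated measures ANOVA of weeks 6 and 12 and adds: "An intention-to-treat analysis will be performed so that the integrity of the randomization is ensured". The sample size section allows for 15% loss of data. It does not say when the loss occurs, in which arm, or why.

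**The concern.** A patient who leaves before week 6 contributes a baseline pain score and nothing more. A repeated measures ANOVA of weeks 6 and 12 cannot include that patient. No later choice of model or imputation method can use a pain rating that was never taken. This is a feature of the data-collection schedule, so an analysis plan cannot supply it.

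The protocol itself gives a reason to think that early loss could be linked to response. In the background it says of sensitized patients: "In these patients an adverse effect of tens on the pain perception can be expected". These are the patients whom the second aim is about. If loss depends on how pain has moved since baseline, the week-6 and week-12 comparisons are made among patients selected on response. Ratings taken shortly before a patient leaves would let the analysis account for that selection.

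**Working it through.** **1. The plan's own numbers.** With a difference of 2.9, SD 4.7, two-sided alpha 0.05 and power 0.80 (sidedness is not stated, but two-sided reproduces the figure):

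- n per arm = 2 × [4.7 × (1.960 + 0.842) / 2.9]² = 41.2, so 42, as stated.
- 42 / 0.85 = 49.4, so 50, as stated.
- 50 × 1.2 = 60 per arm, 120 in total, as stated.
- 15% of 60 is 9 per arm (18 of 120). The remaining 51 per arm give power of 0.87 to 0.88 for 2.9 points.

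Power is adequate after the planned loss, so the question is bias.

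**2. What drives the bias.** Let d be the share of an arm lost before week 6. Let g be how much worse the pain change is in leavers than in completers of that arm. For a completers-only analysis,

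overstatement of TENS benefit = d(TENS) × g(TENS) − d(sham) × g(sham).

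If selection occurred on TENS alone and completers showed a 2.9-point benefit:

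- d = 0.05, g = 2.9: 0.145 points.
- d = 0.15, g = 2.9: 0.435 points (2.9 against 2.465 in all randomised, 18%).
- d = 0.15, g = 5.8: 0.87 points (2.9 against 2.03, 43%).

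These figures set the sham term to zero. If patients whose pain worsens tend to leave, sham patients leave for that reason too, and the second term offsets the first or exceeds it.

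**3. Simulation with selection in both arms.** None of these inputs is in the article: 60 per arm; pain SD 2.2 (the article plans with 4.7); correlation 0.6 between visits; 40% sensitized; 15% lost after week 2 or week 4, with log-odds of loss rising by 0.4 to 1.2 per point of worsening. There were 1500 replicates per scenario. The estimate is the baseline-adjusted week-6 difference (TENS minus sham, negative favours TENS) in patients with a week-6 score.

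True effects: 0.6 × (−2.0) + 0.4 × 0.5 = −1.00; 0.6 × (−2.0) + 0.4 × 1.5 = −0.60; and a uniform −2.9.

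| TENS effect in non-sensitized / sensitized | True | Bias, effect building up gradually | Bias, full effect already at week 2 |
|---|---|---|---|
| −2.0 / +0.5 | −1.00 | overstated by 0.04 to 0.05 | overstated by 0.06 to 0.09 |
| −2.0 / +1.5 | −0.60 | overstated by 0.10 to 0.18 | overstated by 0.16 to 0.30 |
| −2.9 / −2.9 | −2.90 | understated by 0.05 to 0.14 | understated by 0.06 to 0.21 |

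The standard error is about 0.4. If loss is unrelated to response, the bias is nil. If only half of the 15% leaves before week 6, the estimates are about −1.02 for a true −1.00, and −0.68 to −0.74 for a true −0.60.

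**4. Does adding week-2 and week-4 ratings help?** It depends on the model.

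- With common slopes in both arms (the usual likelihood model with one covariance matrix), a bias of 0.04 to 0.07 remains for a true −1.00, which is little or no gain. For a true −0.60, 0.07 to 0.14 remains.
- With arm-specific slopes, the estimates return to about −1.00 and −0.60. The standard error is 0.41 to 0.43, against 0.40 for completers only.

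If TENS helps some patients and harms others, early scores predict later ones more strongly on TENS than on sham, and a common slope misses this. The simulation also lets loss depend only on observed week-2 and week-4 scores, which favours the remedy.

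**The case against.** The strongest reply is that nothing here is an error. The abstract, the follow-up section and the analysis section agree on weeks 6 and 12, the effect is meant to be judged after the six-week course, and handling of missing data is normally left to an analysis plan. This stands as far as it goes, and the point is therefore put as an improvement. It does not remove the gap, because an analysis plan cannot create ratings that were not collected.

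A reader might infer that patients who worsen on TENS will drop out and make TENS look better than it is, by 20 to 40% or by as much as 0.9 points. The article does not support that. It nowhere says that patients who worsen will leave. The Discussion tempers the expected harm, noting that opioid pathways may be less exposed to it. With the protocol's own planning effect of 2.9 points in everyone, loss driven by worsening falls mainly on sham and TENS is understated. The 0.9 figure needs the whole 15% to leave TENS early, a 5.8-point gap, and no selection on sham. Patients who stop the device but attend week 6 are still measured.

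The Discussion also mentions a diary, whose contents are not listed, so pain might be recorded there. No pain item is stated; if one exists, saying so would answer much of this point.

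Finally, the randomization and blinding section separates the researcher who measures from the one who informs patients about treatment, and staff for the device visits are not named. Self-completed ratings respect that separation.

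**Conclusion.** The point holds as a cheap improvement. It is certain from the text that KPa and KPp have no scheduled rating between baseline and week 6, although all patients are asked back twice in that interval, and that the planned ANOVA cannot use anyone lost before week 6.

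The consequence is conditional on early loss depending on pain response. Under the assumptions shown, TENS is overstated by roughly 0.05 to 0.2 points if sensitized patients worsen on it, and understated by roughly 0.05 to 0.15 points if it works uniformly by 2.9 points. If the effect is already complete by week 2, the upper ends rise to about 0.3 and 0.2. Most of these biases are well below half a standard error of about 0.4. They matter most where the true effect is small: 0.10 to 0.18 on a true 0.60 is 17% to 30%. Neither the direction nor the size can be fixed from the article.

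**What to change.** - **Interventions and Follow up:** state that each patient self-completes the KPa and KPp ratings at the existing week-2 and week-4 visits, on the same form as at the other assessments and before the device check.
- **Data reduction and Statistical analysis:** analyse KPa and KPp with a longitudinal likelihood model that keeps partial data (arm by visit, baseline included) and lets covariance or slopes differ by arm. Arm-specific multiple imputation is an alternative. Keep the primary contrast at its stated visit; the added ratings serve only to inform the analysis about patients lost before week 6.

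Both parts are needed: added ratings in a complete-case ANOVA would change nothing, and a common-slope model recovers only part of the bias if response differs between subgroups.

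The cost is two 0-10 items at each of two planned visits, slightly more data entry and a slightly larger standard error. No new visit or patients are required and the total of 120 is unchanged. Patients lost before week 2 would still have no post-baseline score.

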### Equipment

#### Composition and dosing

The settings of the current: burst tens with pulse width of 250 μsec; internal frequency: 100 Hz; burst frequency 3 Hz; intensity: until an unpleasant but non-painful sensation is acquired. The tens devices (ELPHA II 3000, FH Service) to be used will be pre-set with the current settings. Subjects will be taught how to switch on and off the device and how to augment the intensity (mA) of the burst tens current. Patients will be asked not to change the current settings. The electrodes will be placed in the dermatome L4 at 10 cm above the knee. Potential adverse effects may be irritation of the skin near the electrodes.

### Outcome assessment

#### Primary outcome variable

The change from baseline to final assessment of the study knee in the continuous variables *"overall average knee pain" (KPa) and "peak pain over the last 24 h" (KPp*) will be measured using a numeric rating scale [32].

#### Secondary outcome variables

The change from baseline to final assessment of the study knee in *self-reported knee pain and difficulty with physical function *will be measured using the WOMAC Index [32].

The *global perceived effect *(GPE) compared to baseline will be measured on an ordinal scale (1 - much worse, 2 - slightly worse, 3 - no change, 4 - slightly better, 5 - much better) [35]. The GPE is an overall measurement of the perceived effect of the patient. It has been used in various studies to assess therapeutic effects [36-38].

The change from baseline to final assessment of *medication use *will be recorded as another pain variable.

*Pressure pain threshold, temporal summation (TS) and *Diffuse noxious inhibition control (DNIC) will be used as baseline variables.

### Follow up

During the 6 weeks following the first appointment, a study nurse will contact the participants of the tens and stens groups weekly by telephone. Subjects will be asked about any inconvenience with the handling of the tens device as well as if they have received other treatments.

After 6 and 12 weeks participants will be asked to rate their GPE, as well as KPa, KPp, WOMAC and medication use. At these occasions *Pressure pain threshold, temporal summation (TS) and *Diffuse noxious inhibition control (DNIC) will be assessed as well.

### Data reduction and Statistical analysis

An intention-to-treat analysis will be performed so that the integrity of the randomization is ensured. Normality will be checked via the Shapiro-Wilk test.

To ensure good balance of participant characteristics in each group at baseline, stratification is used [39]. Changes in differences between both treatment groups after the intervention period (at 6 w and 12 w) will be analyzed using repeated measures ANOVA for the following variables: KPp, KPa, WOMAC subscores for pain and function, GPE. If the modulus of the partial correlation of potential confounding factors age and sex with the primary outcome values equals minimum 0.3, these covariates of prognostic values will be added as covariates in the ANOVA model [40].

As a secondary analysis, a linear regression analysis will be used with the following dependent factors: BMI, TS and DNIC; and as independent factors: KPa, KPp, WOMAC subscales for pain and function.

Significance value for all tests will be set at p < 0.05. All analyses will be performed using SPSS 20 for Windows.

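### The plan promises intention-to-treat but names a repeated measures ANOVA that in its ordinary form drops patients with a missing visit, and it does not name the term or visit that tests the primary outcome

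*Protocol article*

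**What the plan says.** All references are to the protocol article.

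- **Data reduction and Statistical analysis**, population: "An intention-to-treat analysis will be performed so that the integrity of the randomization is ensured".
- **Same section**, method: between-group differences "at 6 w and 12 w) will be analyzed using repeated measures ANOVA for the following variables: KPp, KPa, WOMAC subscores for pain and function," and GPE. The software sentence reads "All analyses will be performed using SPSS 20 for Windows"; no SPSS procedure is named.
- **Sample size**: "To take into account a 15% loss of data sample size is inflated up to 50 per group (n/0.85". The total is then raised to 120.
- **Primary outcome variable**: "The change from baseline to final assessment of the study knee in the continuous variables" average and peak knee pain (KPa and KPp).
- **Follow up**: "After 6 and 12 weeks participants will be asked to rate their GPE, as well as KPa, KPp, WOMAC and medication use". With baseline, that makes three time points for pain and WOMAC. GPE is rated against baseline and so has no baseline value.

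The statistical section names no main effect, interaction or contrast as the primary test, and does not say whether week 6 or week 12 is the final assessment.

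**The concern.** Intention-to-treat is promised for a stated reason: to keep the comparison that randomization created. Classical repeated measures ANOVA (in SPSS, the GLM Repeated Measures procedure) works on one complete row per patient and deletes incomplete rows. Claim and method then pull apart, in a trial that itself expects data to be lost. If patients with little relief leave one arm more often than the other, the patients left are no longer the randomized groups and the estimate can be biased.

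The second part concerns what is tested. The primary outcome is one change score per patient for each pain variable, and the sample size compares two means. A repeated measures ANOVA offers several tests, which answer different questions. Left open, the choice could be made after the data are seen.

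**Working it through.** **1. Reproduce the plan's figures.** Inputs from the sample size section: difference 2.9, SD 4.7, alpha 0.05 (two-sided assumed), power 0.80.

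- n per group = 2 × (1.960 + 0.842)² × 4.7² / 2.9² = 2 × 7.85 × 22.09 / 8.41 ≈ 41.2, so 42. This agrees.
- 42 / 0.85 = 49.4, so 50. This agrees.
- 50 × 1.20 × 2 = 120. This agrees.

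**2. Patients deleted.** If 15% of patients lack a needed visit, 60 × 0.85 = 51 per group remain. That is 102 analysed and 18 excluded. If instead (assumption) each of the two follow-up visits is missed independently:

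| Loss per visit | Complete patients per group |
|---|---|
| 5% | 60 × 0.95² ≈ 54 |
| 10% | 60 × 0.90² ≈ 49 |
| 15% | 60 × 0.85² ≈ 43 |

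**3. Does this break the sample size?** No. At 51 per group, 2.9 / (4.7 × √(2/51)) = 3.12, so power = Φ(3.12 − 1.96) ≈ 0.876 (0.870 by the t distribution). At 60 per group it is 0.922 (0.918). Even 43 per group gives 0.807.

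**4. Bias from deletion.** Illustration with assumed dropout patterns: no true effect, 60 per arm, SD of change 4.7, correlation 0.5 between the week-6 and week-12 changes, 20,000 simulated trials.

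| Who is lost (15%) | Bias at week 12 | Type I error |
|---|---|---|
| Random in both arms | about 0 | 0.049 |
| Worst week-6 responders in both arms | about 0 | 0.057 |
| Worst week-6 responders in active arm, random in sham | 0.63 | 0.113 |

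A hand check of the third row: 0.5 × 4.7 × 0.233 / 0.85 ≈ 0.64, where 0.233 is the normal density at the 15% cut.

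A second set of assumptions had a true difference of 1.5, SD 2.5, correlation 0.5, and about 15% dropout driven by week-6 pain (20% sham, 9% active). Completer differences in raw scores were 1.14 at week 6 and 1.34 at week 12. An estimate using all week-6 data recovered 1.51 at week 12. On change scores in that same simulation the completer figure was 1.32 at week 6, with about no bias at week 12. The size, and even the presence, of bias thus depends on the mechanism and on the score analysed.

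**5. Which test?** Power at 51 per group with the plan's 2.9 (taken as the week-12 effect) and 4.7 (as the SD of change), assuming equal correlations of 0.5 between visits:

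| Possible reading | Week-6 effect equal | Week-6 effect half |
|---|---|---|
| Change to week 12, 1 df | 0.87 | 0.87 |
| Group × time over three visits, 2 df | 0.90 | 0.79 to 0.80 |
| Group effect averaged over three visits | 0.71 | 0.47 |
| Group effect over weeks 6 and 12 only, 1 df | 0.95 | 0.77 |

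The last row is a normal approximation. The SD of a two-visit mean is 4.7 × √0.75 = 4.07, and its standard error is 4.07 × √(2/51) = 0.806. Then 2.9 / 0.806 = 3.60 gives Φ(1.64) ≈ 0.95, and 2.175 / 0.806 = 2.70 gives Φ(0.74) ≈ 0.77. If the week-6 effect is zero, the 2-df test has about 0.90. The readings differ in what they test, and none is uniformly weaker than the planned change contrast except the average that includes baseline.

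**The case against.** The strongest reply is that the text does not settle how missing visits are treated. SPSS also has a MIXED procedure that keeps partial data, and imputation before the ANOVA would keep everyone. A condensed article commonly leaves missing-data rules to the full protocol or analysis plan, so their absence alone is no finding. This stands, and it makes the point conditional. It does not remove it, because the article names a method whose ordinary meaning conflicts with the population it claims.

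Three stronger readings are tempting and are not supported:

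- *The n/0.85 inflation confirms a completers analysis.* It does not. Inflating for loss is routine under any method and says nothing about how missing visits will be analysed.
- *An omnibus test, or one diluted by baseline, replaces the primary contrast.* Neither is in the text. Because the same ANOVA covers GPE, which has no baseline value, a two-visit ANOVA on weeks 6 and 12 with a 1-df group effect is at least as natural a reading.
- *The method loses power.* Under one set of assumed inputs (51 per arm, SD 2.5, correlation 0.5, constant effect 1.4), the change contrast has about 80% power, group × time 83%, and a two-visit group effect about 90%. A loss appears only against a baseline-adjusted week-6 analysis (89%), which is planned nowhere, or under the reading that averages in baseline.

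**Conclusion.** The point holds as a mismatch between the promised population and the named method, together with an unnamed primary term and visit. Read in its ordinary sense, repeated measures ANOVA would exclude about 18 of 120 randomized patients, assuming that the 15% loss means patients lacking a needed visit. Bias follows only if loss relates to pain. It ranged from none under random loss to about 0.63 points, with type I error about 0.11, under one assumed arm-specific pattern; the documents give no dropout pattern to choose between these. The sample size stands, and a general loss of power is not shown. It would go too far to say that the trial will certainly be analysed on completers, since a mixed procedure or imputation could still deliver what is promised.

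**What to change.** For KPa, KPp and the WOMAC subscores, replace repeated measures ANOVA by a likelihood-based linear mixed model (SPSS MIXED).

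- **Data:** week-6 and week-12 values of all randomized patients with at least one follow-up, analysed in the group assigned.
- **Fixed effects:** treatment, visit, treatment × visit and the baseline value.
- **Primary test:** state which visit is the final assessment and name the treatment contrast at that visit as the one primary test for each pain variable.
- **Sensitivity analysis:** one that departs from missing at random and covers patients with no follow-up value, whom this model still leaves out.

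Other methods that keep partial data, such as imputation before the ANOVA, would also remove the conflict if they are written down.

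The cost is analysis wording and slightly more analysis work in the same software, with no new data and no change to the 120 patients. The model relies on missing at random, which the data cannot verify; hence the sensitivity analysis.

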#### Knee pain and physical function

Overall average knee pain (KPa) and peak pain intensity over the last 24 h (KPp) will be assessed by a 11-point numeric rating scale with terminal descriptors of 0 = no pain; 10 = maximal pain [32]. Self-reported knee pain and difficulty with physical function will be measured using the Western Ontario and McMaster Universities (WOMAC) Index [32].

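### Global perceived effect is already a rating of change and exists only at weeks 6 and 12, so the repeated measures ANOVA contrast named for it does not fit, and the protocol does not designate the between-group term that would

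*Protocol article*

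**What the plan says.** Under Secondary outcome variables, GPE is "compared to baseline will be measured on an ordinal scale (1 - much worse, 2 - slightly worse, 3 - no change", continuing up to slightly and much better. The Follow up section fixes when it is collected: "After 6 and 12 weeks participants will be asked to rate their GPE, as well as KPa, KPp, WOMAC and medication use". The baseline sections do not list GPE, and could not, because each rating is itself a comparison with baseline. The pain scores and WOMAC do have baseline values; for pain, for example, "Overall average knee pain (KPa) and peak pain intensity over the last 24 h (KPp) will be assessed by a 11-point numeric rating scale" under Baseline measurements.

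Data reduction and Statistical analysis then gives one analysis for all of them: "Changes in differences between both treatment groups after the intervention period (at 6 w and 12 w) will be analyzed using repeated measures ANOVA". GPE stands last in the list of outcomes attached to that sentence, after both pain scores and the two WOMAC subscores. On distribution the section says "Normality will be checked via the Shapiro-Wilk test", and on the error rate "Significance value for all tests will be set at p < 0.05". It names no separate contrast, visit or method for GPE.

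**The concern.** For an outcome measured at baseline, a treatment effect shows up as a change over time in the gap between arms, so a group-by-time contrast addresses the trial's question. GPE has no baseline value. With two post-baseline visits, the same contrast compares the gap at week 12 with the gap at week 6. Stimulation lasts 6 weeks, so for GPE this asks whether the gap changes after treatment ends, not whether tens does better than sham.

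An analyst who reports that term as the GPE result would find nothing when a benefit is steady, and could find a significant result only because a benefit was lost. An analyst who reports the main effect instead would be answering the right question, but with a term that the protocol did not designate. A lesser concern is that a variable the protocol itself calls ordinal is given a normal-theory method.

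**Working it through.** **The plan's own figure.** The Sample size section uses a difference of 2.9, SD 4.7, power 0.80 and alpha 0.05 (two-sided assumed, since sidedness is not stated).

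- n per arm = 2 × (1.960 + 0.842)² × (4.7/2.9)² = 2 × 7.85 × 2.627 = 41.2, rounded up to 42. Power by the t distribution at 42 per arm is 0.798.
- 42/0.85 = 49.4, rounded up to 50 per arm.
- 50 × 1.2 × 2 = 120 in total.

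The stated 42, 50 and 120 are reproduced. They concern pain; the protocol gives no figure for GPE. With 15% loss, 120 × 0.85 / 2 = 51 evaluable patients per arm.

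**The contrast, by algebra.** Let d6 and d12 be the mean tens-minus-sham differences in GPE at weeks 6 and 12.

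- Group-by-time term: d12 − d6.
- Between-group main effect: (d6 + d12)/2.
- Constant benefit, d6 = d12 = d: the first is 0 and the second is d.
- Benefit gone by week 12, d6 = d and d12 = 0: the first is −d and the second is d/2.

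For an outcome with a baseline value, the expected differences at the three times are 0, d and d. Their mean is 2d/3, so they deviate from it by −2d/3, d/3 and d/3. The group-by-time term is therefore not zero under a constant benefit.

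**Simulation on a five-category scale.** Assumptions not in the protocol:

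- latent normal ratings cut at −1.5, −0.8, 0.3 and 1.2 SD;
- within-patient correlation 0.3, 0.5 or 0.7;
- the same latent shift at both visits, 2.9/4.7 = 0.617 SD, borrowed from the pain calculation (about 0.59 GPE points);
- 4000 runs per cell.

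Rejection rates at 51 per arm:

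| Correlation | Group-by-time | Between-group main effect | Week 12, t test | Week 12, Mann–Whitney |
|---|---|---|---|---|
| 0.3 | 5.6% | 95.7% | 83.2% | 82.2% |
| 0.5 | 5.2% | 92.9% | 83.4% | 82.2% |
| 0.7 | 4.7% | 89.2% | 83.5% | 82.4% |

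At 42, 51 and 60 per arm taken together, the group-by-time rate stays between 4.6% and 5.6%. This follows by construction: the contrast is zero, so a valid test rejects at alpha.

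**Comparison.** A simulated continuous outcome with a baseline value and the same constant shift, 51 per arm, gives group-by-time power of 78%, 90% and 99% at correlations 0.3, 0.5 and 0.7. The misfit is therefore specific to GPE.

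**The case against.** The stronger reading is that the planned ANOVA cannot detect a steady benefit on GPE. A reader might infer this, but the protocol does not support it. The analysis section names a model and never uses the word interaction. A repeated measures ANOVA with a group factor also gives a between-group main effect, and in the table above that term detects a constant benefit in 89% to 96% of runs.

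The sentence can also be read more kindly. It may mean between-group differences in change, looked at on each visit. The outcome sections define pain and WOMAC as changes from baseline, and GPE is already such a change. On that reading, the GPE analysis is close to the direct comparison wanted here. Nothing in the document says that a null group-by-time result would be reported as no effect.

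It can further be said that naming model terms belongs in a statistical analysis plan, which is not shown. The ordinal point is also small: the t test and Mann–Whitney differ by about one percentage point of power.

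Most of this stands, and it limits the claim to the named contrast. It does not remove the point. The article does state an analysis for GPE by name, in wording shared with outcomes of a different structure. Its most literal reading gives a test that does not address treatment benefit, and no other term is designated. The Shapiro–Wilk check does not repair that.

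**Conclusion.** The point holds in a limited form. Read as group-by-time, the stated contrast does not test benefit on GPE: under a constant difference it rejects at about 5%, a result that needs no assumption about scale, correlation or sample size. The between-group effect in the same model would serve but is not designated. The 89% to 96% and the 82% to 84% for a week-12 comparison rest on the assumed shift, cut-points and correlations, and are illustrations only. No power is quoted for a benefit that fades by week 12, because it depends heavily on the unknown within-patient correlation.

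The use of ANOVA on a five-point scale is the lesser part. A reader should not infer that the main trial result is at risk: GPE is secondary, the primary pain scores have baseline values, and the sample size reproduces.

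**What to change.** Take GPE out of the list of variables in the repeated measures ANOVA sentence and give it its own sentence: the arms are compared on GPE at week 6 and, separately, at week 12, by a proportional-odds model with sex and age as covariates, or by a Wilcoxon rank-sum test stratified by those two randomisation factors. Report a common odds ratio (from the proportional-odds model) and, by arm, the proportion rating themselves slightly or much better.

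The new sentence should say that sex and age enter the GPE analysis regardless of the 0.3 partial-correlation rule, which is written for the ANOVA and the primary outcomes. Sex by five age categories makes 10 strata, some probably small, which favours the model over the stratified test.

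If the team prefers to keep the ANOVA, the minimum change is to designate the between-group effect, not group-by-time, as the GPE test.

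The cost is one or two sentences in the analysis section, with no change to data collection, visits or sample size. It should be made before the data are unblinded, so that the choice of term is not open to question.
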